### Data management and confidentiality

All data will be entered electronically by two independent student assistants. Any deviations will be clarified and corrected. Original study forms will be kept on file. All study-related information is stored in a secure and accessible place and manner. All participant information will be stored and locked in file cabinets in areas with limited access. Participant files will be kept in storage for a period of 3 years after completion of the study. Blood samples will be disposed after analyses.

All laboratory samples, reports, data collection, process and administrative forms will be identified by a coded identification number, to maintain participant confidentiality. All records that contain names or other personal identifiers, such as locator forms and informed consent forms, will be stored separately from study records, which are also identified by code numbers. All local databases will be secured with password-protected access systems. Forms, lists, logbooks, appointment books and any other listings that link participant identification numbers to other identifying information will be stored in a separate, locked file in an area with limited access.

### Sample size calculation

Sample size calculation was done for the effect of experimental treatment (WBV-training vs. PCG intervention) on the primary endpoint (severity of depression symptoms) measured by CDRS-R raw-scores in an *analysis of covariance* (ANCOVA) model using G*Power 3.1.9.2 software [52]. It was hypothesized that changes in the CDRS-R raw-scores from baseline to completion of the 6-week intervention differ significantly between the WBV-training group and the PCG-training group. As clinically relevant effect size, a medium effect of *d* = .5 was defined. Alpha was set at 5%. Test power (1 − *β*) was set at 80%. Participants’ CDRS-R scores at baseline will be included in the model as covariate. Required sample size in such an ANCOVA model can be calculated as (1 − *ρ*^2^) × *n*, with *ρ* representing the correlation between participants’ baseline and post-treatment outcome scores, and *n* representing the sample size that would have been required if a *t* test of post-treatment outcome scores was applied [53]. Based on the results of our pilot study, we estimated the correlation between patients’ severity of depression symptoms at baseline and at post treatment with *ρ* = .6. Under the presuppositions made, sample size calculation showed that 41 patients in each group (*N* = 82) would be required. We accounted for a 15% dropout rate, leading to a total sample size of *N* = 94 patients.

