**Methods/design:**

A double-blinded randomized controlled trial is conducted at the University Hospital of Cologne in Germany, comparing a 6-week, whole-body vibration strength-training with a 6-week placebo-intervention, as add-on therapy to inpatient treatment as usual. Forty-one subjects (13–18 years of age) will be included in each of the two groups. The study is powered to detect (*α* = .05, *β* = .2) a medium effect size difference between the two groups (*d* = .5) in terms of patients’ change in the Children’s Depression Rating Scale raw-score, from baseline until the end of the intervention. As secondary endpoints, the effects of exercise treatment on patients’ cortisol awakening response as well as on brain-derived neurotrophic factor, insulin-like growth factor 1 and inflammatory markers (tumor necrosis factor-alpha, interleukin-6 and C-reactive protein) serum levels will be assessed.

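### The 15% dropout allowance is added to the required 82 instead of divided out, so the stated total of 94 falls about 2 evaluable patients short (minor)

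*Protocol article*

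**What the plan says.** The section "Sample size calculation" of the protocol article sets out the inputs. On the effect: "As clinically relevant effect size, a medium effect of *d* = .5 was defined". Alpha is 5% and power 80%. For the covariate adjustment, "we estimated the correlation between patients’ severity of depression symptoms at baseline and at post treatment with" ρ = .6, and the t-test sample size is multiplied by (1 − ρ²). The result: "sample size calculation showed that 41 patients in each group" (N = 82) would be required. The dropout step follows directly: "We accounted for a 15% dropout rate, leading to a total sample size of" N = 94.

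The abstract (Methods/design) gives a number without a dropout allowance: "Forty-one subjects (13–18 years of age) will be included in each of the two groups". Its next sentence states the α, β and effect size for which the study is powered. The abstract does not mention 94.

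**The concern.** A dropout rate is a fraction of those who enter the trial. To finish with 82 evaluable patients after losing 15%, the required number must be divided by the fraction retained, 0.85. Adding 15% of 82 to 82 gives a smaller number, and it covers a smaller loss than the one stated. The 94 therefore does not deliver the 82 that the sentence before it calls for.

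Two things are at stake. The first is a slight shortfall in evaluable patients and power at the protocol's own dropout rate. The second is clarity about the target: the abstract speaks of 41 per group being included, while the sample size section arrives at 94. The article also says (Methods/design) that changes in sample sizes need a formal amendment, so the planned number should be the same wherever it appears.

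**Working it through.** **Inputs** (all from "Sample size calculation"): d = .5; α = .05; power .80; ρ = .6; 1:1 allocation; dropout 15%. The test is taken as two-sided. The article does not say so outright, but the hypothesis is non-directional: the changes "differ significantly between the WBV-training group and the PCG-training group".

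**Step 1: reproduce the required number.**
- A two-sided two-sample t test with d = .5 needs 64 per arm (power 80.1%, non-central t).
- ANCOVA factor: 1 − ρ² = 1 − .36 = .64.
- 64 × .64 = 40.96, so 41 per arm and N = 82. This matches the article.

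**Step 2: reproduce the inflated total.**
- Adding 15%: 82 × 1.15 = 94.3, rounded down to 94. This matches the article.
- Dividing by the fraction retained: 82 / (1 − .15) = 82 / .85 = 96.47, so 97. Per arm: 41 / .85 = 48.2, so 49 and a total of 98.
- Rounding 96.5 cannot give 94, so the article used the additive form.

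**Step 3: check forwards.**
- 94 × .85 = 79.9, about 80 evaluable (40 per arm), against 82 required.
- Loss that 94 can absorb: (94 − 82) / 94 = 12 / 94 = 12.8%.
- 97 × .85 = 82.5 and 98 × .85 = 83.3; both reach 82.

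**Step 4: power at 41 and at 40 per arm**, each line comparing like with like:
- The protocol's route (t test on n / .64): 41 per arm corresponds to the 64 per arm of step 1, power 80.1%. 40 per arm corresponds to 40 / .64 = 62.5, power 79.2%.
- Non-central t with ANCOVA degrees of freedom (effect .5 / √.64 = .625, df = 2n − 3): 79.8% at 41 and 78.8% at 40.
- Normal approximation: 80.8% at 41 and 79.8% at 40.

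By each method the loss is about one percentage point.

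**The case against.** The strongest reply is that this hardly matters. Two patients and one point of power are small beside the softness of the inputs: d = .5 is a conventional medium effect, and ρ = .6 comes from a pilot that, by the article's own account, relied on self-report and not on the CDRS-R. The shortfall also arises only if loss exceeds 12.8%. This stands, and it is why the point is minor. It does not make 94 the right result for the stated inputs.

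A second reply is that dropout is not defined as a missing post-treatment CDRS-R. The analysis is by intention to treat, and a patient who stops training may still be rated. At 15% treatment dropout the evaluable number could then lie anywhere from 80 to 94. This also stands, as a condition on the figure of 80. But the plan adds patients to make up for dropout, so its own calculation treats them as lost.

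Third, the abstract's 41 per group equals the powered number in the sample size section, and the sentence after it is about power. It is most naturally read as the evaluable number, loosely worded. That is fair, and it leaves only a labelling correction.

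**Conclusion.** Wrong as written, and minor. The base of 82 is right; the error lies only in the dropout step. If 15% of 94 randomised patients contribute no post-treatment CDRS-R score, about 80 remain, 2 short of 82, and power falls by about one percentage point. This rests on a two-sided test, the article's d and ρ, and dropout meaning a missing primary outcome.

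Two stronger readings are tempting but not supported:

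- A reader might infer that the plan misses 80% power because 40 per arm gives 78.8%. That sets an ANCOVA-based figure against a target reached by the t-test route. By the ANCOVA method even the full 41 per arm gives 79.8%, so part of the gap comes from the change of method and not from the dropout step.
- A reader might take the abstract's 82 as a rival enrolment target: 82 × .85 = 69.7, about 35 per arm, with power of about 73%. But the sample size section sets 94 with a dropout allowance, and nothing in the article says recruitment stops at 82. The 73% describes a plan that the article does not set.

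**What to change.** Use one randomisation target throughout and make the claim fit it. There are two ways:

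- Keep 94 and restate what it provides: 94 randomised, about 80 evaluable at 15% dropout, power about 79%; or say that 94 allows for 12.8% dropout. This changes text only, and the stated power becomes slightly less favourable.
- Correct the total to 97, or 98 for equal arms. This means 3 or 4 more patients and, by the article's own rule on changes in sample size, a formal amendment. Recruitment was still open at publication, with completion expected by 31 July 2020.

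In either case, change the abstract so that 41 per group is labelled as the evaluable number required, and give the randomisation target from the sample size section beside it. The design and the analysis are unaffected.

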### Statistical analysis

An intention-to-treat analysis will be performed. We will also assess the effect of the complete treatment in a per-protocol analysis. To determine the effects of between-subjects factor “treatment,” within-subjects factor “measurement time point” and their interaction on primary and secondary outcomes, separate 2 × 3 (hypothesis A, E, F)/2 × 2 (hypothesis C, D) mixed ANCOVAs will be conducted. For secondary outcome “HPA axis activity” (hypothesis B) separate 1-factor ANCOVA will be conducted. As covariate, patients’ baseline scores of each specific parameter will be used. A significant main effect of within-subjects factor measurement time point will be further investigated through post hoc pairwise comparisons. Simple effects analyses will be conducted to determine potential group differences at each time point. Due to the exploratory character of the secondary hypotheses, alpha error adjustment will not be applied.

ANCOVA assumptions will be explored. In case of violations of normality assumption, appropriate non-parametric procedures will be used. In case of violations of ANCOVA assumptions of homogeneous variances for between-subjects factor levels and sphericity for variances of differences between categories of within-subjects factor, the F-test will be adjusted. Eta-squared values will be reported as effect size estimates for explained variance, and Cohen’s *d* values will be reported for post hoc pairwise comparisons.

Statistical analysis will be performed by a statistician, blinded to treatment groups. Statistical analyses will be conducted using SPSS 25® (IBM®, Armonk, NY, USA). A result will be considered significant at a *p* value equal to or less than .05.

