### Primary endpoint

The primary endpoint of the present study is patients’ change of severity of depression symptoms from baseline until the end of the 6-week intervention. Patients’ severity of depression symptoms is measured by the CDRS-R. In the context of clinical trials, the CDRS-R is one of the most frequently used clinician ratings for the assessment of depressive symptomatology in adolescents [45]. The CDRS-R is a semi-structured interview consisting of 17 items that are rated between 1 (“no difficulties”) and 5 or 7 points (“clinically significant difficulties”). Usually, a raw-score of 40 points is used as a cut-off for depressive symptomatology and higher raw-scores are interpreted as more severe depression symptoms [43]. For CDRS-R application in adolescents, excellent internal consistency and good convergent validity have been reported [45].

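### The primary test at the end of treatment is read from a three-visit repeated-measures ANCOVA which, unless missing scores are imputed first, leaves out patients with an observed t1 score who miss a later visit, contrary to the intention-to-treat promise

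*Protocol article*

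**What the plan says.** All references are to the protocol article.

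- **Endpoint.** The Primary endpoint section defines it as "change of severity of depression symptoms from baseline until the end of the 6-week intervention". Hypothesis A in Table 1 covers the same interval. The visits at 8 weeks (t2) and 20 weeks (t3) after treatment belong to hypothesis F.
- **Analysis set.** Statistical analysis: "An intention-to-treat analysis will be performed", with a per-protocol analysis in addition.
- **Model.** Same section: "separate 2 × 3 (hypothesis A, E, F)/2 × 2 (hypothesis C, D) mixed ANCOVAs will be conducted". On the covariate: "As covariate, patients’ baseline scores of each specific parameter will be used".
- **Type of test.** If the assumptions of equal variances or sphericity fail, the remedy is an adjusted F-test: "sphericity for variances of differences between categories of within-subjects factor, the F-test will be adjusted". Eta-squared is the effect measure. On software: "Statistical analyses will be conducted using SPSS 25".
- **Group comparison at each visit.** "Simple effects analyses will be conducted to determine potential group differences at each time point". No separate t1 analysis is described for hypothesis A.
- **Sample size.** The Sample size calculation section uses an ANCOVA of the post-treatment score with baseline as covariate, at one time point. It gives 41 per group, then adds: "We accounted for a 15% dropout rate", for a total of 94. It does not say which visit the 15% refers to.

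**The concern.** The primary question is about one visit, but the model that answers it spans three. A classical repeated-measures ANCOVA needs a complete set of outcomes from each patient. A patient who was randomised, was treated and has a CDRS-R score at t1 contributes nothing if the t2 or t3 score is absent, unless that score is filled in beforehand. Neither later visit is part of the primary endpoint.

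Two things are at stake. First, observed primary outcomes are discarded and power falls. Second, the analysed patients are selected by something that happens after randomisation and after t1. Training takes place during the inpatient stay, whereas t2 and t3 fall weeks later and have a window of ± 3 days. If attendance at those visits is related to how the patient was doing at t1, the t1 comparison is no longer the one that randomisation protects.

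**Working it through.** **1. Which visits are in the model.** CDRS-R is measured at enrolment (serving as baseline), t1, t2 and t3. Baseline is the covariate, so the three levels of the time factor are t1, t2 and t3. The other models fit this reading: hypotheses C and D (blood markers at t1 and t2) get 2 × 2, and hypothesis B (cortisol at t1 only) gets a one-factor ANCOVA. The t1-only secondary outcome thus has a t1-only model, and the t1-only primary outcome does not.

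**2. Which procedure.** Sphericity is an assumption of the classical repeated-measures F-test. A likelihood-based mixed model with unstructured covariance does not make it. With the adjusted F-test and eta-squared, the text describes the classical procedure, which uses complete t1–t2–t3 vectors.

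**3. Reproducing the plan's sample size.** Inputs from the Sample size calculation section: d = 0.5, alpha 5% (two-sided reproduces the figure), power 80%, ρ = 0.6.

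- Two-sample t-test (noncentral t): n = 64 per arm.
- ANCOVA factor: 1 − 0.6² = 0.64, and 64 × 0.64 = 40.96, rounded up to 41 per arm, N = 82. This matches.
- 82 × 1.15 = 94.3, matching the stated total of 94.

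The stated figures are those of a single-time-point t1 ANCOVA.

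**4. Power by number analysed.** Effective effect = 0.5/√0.64 = 0.625. Noncentrality = 0.625 × √(N/4), df = N − 3, two-sided 5%. At N = 82 this gives 79.8%, the planned power.

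Attrition after t1 is not in the documents. The rows below are assumptions, with losses unrelated to outcome.

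| Assumed loss from 94 | Complete at t1, t2 and t3 | Power for t1 contrast |
|---|---|---|
| 15% in total through t3 | 94 × 0.85 = 79.9 | 78.8% |
| 15% by t1, a further 10% after | 79.9 × 0.90 = 71.9 | 74.3% |
| 15% by t1, a further 20% after | 79.9 × 0.80 = 63.9 | 69.1% |
| 15% by t1, a further 30% after | 79.9 × 0.70 = 55.9 | 63.1% |

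In the last three rows 79.9 patients have a t1 score, and using all of them would give 78.8%. The three-visit model sets aside about 8, 16 and 24 of them. In the first row some patients lost before t3 would also have a t1 score. With no loss at all by t1, 94 patients would give 85.0%.

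**5. Bias (illustrative simulation).** True t1 effect 0.5 SD, ρ = 0.6, chance of later loss rising with a worse t1 score (log-odds 1 per SD).

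- Loss unrelated to outcome: the t1 estimate in complete cases stays at 0.50.
- Same pattern in both arms: 0.48, 0.46 and 0.45 at 10%, 20% and 30% loss after t1. With no true effect, no spurious difference appears.
- Pattern in the control arm only, 30% loss: 0.32. With no true effect, a spurious difference of about 0.18 SD appears, against the vibration training.

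**The case against.** The strongest objection is that the article never mentions complete cases or deletion. That step is inferred from the named method. A sphericity-adjusted F-test on imputed data is compatible with every word of the section, and imputation is something a separate analysis plan, not shown here, may well specify. This stands, and it is why the point is conditional. It does not remove the point. The published model is itself mismatched to a t1-only endpoint and to the t1-only sample size, and a better-suited method is available in the same software.

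The size of the harm is also assumed. If the 15% already covers loss through t3, power is within about one percentage point of the planned 80%. With the same informative loss in both arms, the bias is at most about 0.05 SD in these scenarios, towards no effect. The larger biases need dropout that differs between arms, for which the documents give no evidence. All this stands.

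Two stronger readings are tempting and unsupported. A reader might infer that inflating the sample size for 15% dropout itself contradicts intention-to-treat. It does not, because planning for missing outcomes says nothing about the analysis set. A reader might also infer that the 15% cannot cover loss to t3. The article does not say which visit it refers to, so that cannot be asserted.

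**Conclusion.** The concern holds in conditional form. As written, and unless missing scores are imputed first, the primary comparison is confined to patients who also attended 8 and 20 weeks after treatment. That conflicts with the intention-to-treat statement and departs from the analysis for which the trial was sized.

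The cost in power runs from negligible against plan (about 79%, if 15% is the total loss through t3) to substantial (about 63%, if a further 30% is lost after t1). Bias adds to this only if later attendance depends on the t1 score, and it is serious only if that dependence differs by arm. These figures rest on d = 0.5 and ρ = 0.6 from the article and on attrition that the article does not give. It would go too far to conclude that the trial will necessarily discard these patients, since an analysis plan not shown could prevent it.

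**What to change.** State one primary test for hypothesis A that uses every observed t1 score. Either of these would do:

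1. An ANCOVA of t1 CDRS-R on treatment with baseline CDRS-R as covariate, in all randomised patients as allocated, with stated handling of missing t1 scores (for example multiple imputation). This is the analysis behind the sample size.
2. A likelihood-based mixed model (SPSS MIXED) with treatment, visit, treatment × visit, baseline, baseline × visit and unstructured covariance, naming the treatment contrast at t1 as primary. Patients with no post-baseline score add no outcome data here, so the text should say how they are handled.

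The t2 and t3 contrasts for hypothesis F can come from the second model. Keep the complete-case repeated-measures ANCOVA as a sensitivity analysis, and state which visit the 15% dropout refers to.

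The cost is a few sentences and some syntax in the software already named, with no new data. According to the Trial status section recruitment was ongoing and analysis follows its completion, so the change could be made before the data are analysed.

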### Randomization and blinding

Eligible patients are randomized to one of two treatments (see “Groups and treatments” section below). A stratified block randomization with permuted block length is conducted. The stratification factor is patients’ gender (male vs. female). Randomization of treatment groups is implemented based on sealed, opaque envelopes by the Institute of Medical Statistics and Computational Biology of the University of Cologne.

The present study is a double-blinded trial. Prior to participation, patients will be informed that two physical activity interventions (whole-body vibration strength-training/myofascial release training) will be compared regarding their effect on severity of depression symptoms in adolescent inpatients. Accordingly, patients do not know the specific hypotheses of the trial. They will not know if they are allocated to the experimental or to the control group and, therefore, can be considered blinded. Moreover, experimental testing procedures will be carried out by specially trained experimental staff that will also be blinded regarding the allocation of participants to the specific experimental group.

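### Randomisation is stratified by gender but the ANCOVAs adjust only for baseline; if gender is prognostic beyond baseline, the test is mildly conservative and attainable power is forgone

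*Protocol article*

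**What the plan says.** Randomization and blinding: "A stratified block randomization with permuted block length is conducted". The sentence that follows names gender, in two levels, as the stratification factor, and the caption of Fig. 1 repeats this. No other factor is named.

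Statistical analysis: the models contain treatment, measurement time point and their interaction (a one-factor ANCOVA for the cortisol outcome). The covariate rule covers all of them, in that patients' "baseline scores of each specific parameter will be used".

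Sample size calculation: the same single adjustment is assumed, in that participants' CDRS-R "scores at baseline will be included in the model as covariate".

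Gender is in none of these models, is not listed under Potential confounding factors, and no reason is given for leaving it out.

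**The concern.** Stratified blocks force the arms to be nearly equal in gender composition. Gender then contributes almost nothing to the real variability of the treatment difference. A model without gender still counts the gender variance as error, so the reported standard error exceeds the true one. Where gender is related to the outcome after baseline adjustment, p-values come out too large, confidence intervals too wide, and precision that the randomisation has already secured is not used.

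The sample size leaves little margin: 41 per group is the smallest number that meets 80% power under the stated assumptions. The same covariate rule also governs the BDI-II, cortisol, growth-factor and inflammatory outcomes.

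**Working it through.** **Inputs from the Sample size calculation section.** d = 0.5 ("a medium effect of *d* = .5 was defined"); alpha 5%; power 80%; correlation of baseline with post-treatment score 0.6; 41 per group. Sidedness is not stated. The hypothesis is that changes "differ significantly between the WBV-training group and the PCG-training group", so two-sided is used; one-sided would give 32 per group and does not reproduce the plan.

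**Step 1: the plan's own figure.** Unadjusted comparison: n = 2(1.960 + 0.842)²/0.5² = 62.8, so 63 per group (64 with the t distribution). Multiplied by 1 − 0.6² = 0.64 this is 40.3 (41.0), so 41. The stated 41 is reproduced. Power at 41: SE = 0.8 × √(2/41) = 0.1767; 0.5/0.1767 = 2.830; Φ(2.830 − 1.960) = 80.8%.

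**Step 2: assumed size of the gender effect.** Let b be the difference between genders, in SD units, beyond baseline. With an assumed 58/24 split, p(1 − p) = 0.207, and gender contributes variance v = 0.207b²: 0.0186, 0.0518 and 0.1325 for b = .3, .5 and .8.

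**Step 3: gender variance contained in the planned residual variance of 0.64.** Then r² = v/0.64.
- Type I error without gender = 2[1 − Φ(1.960/√(1 − r²))]
- Power without gender = Φ((2.830 − 1.960)/√(1 − r²))
- Power with gender = Φ(2.830/√(1 − r²) − 1.960)

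| b | r² | Type I error without | Power without | Power with | Forgone |
|---|---|---|---|---|---|
| 0 | 0 | 5.0% | 80.8% | 80.8% | 0 |
| .3 | .029 | 4.7% | 81.1% | 81.9% | 0.8 |
| .5 | .081 | 4.1% | 81.8% | 83.9% | 2.1 |
| .8 | .207 | 2.8% | 83.6% | 88.8% | 5.3 |

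**Step 4: gender variance added on top of 0.64.** Then r² = v/(0.64 + v). The type I formula is unchanged; power without gender = Φ(2.830 − 1.960/√(1 − r²)); power with gender stays at 80.8%.

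| b | r² | Type I error without | Power without | Power with | Forgone |
|---|---|---|---|---|---|
| .3 | .028 | 4.7% | 80.0% | 80.8% | 0.8 |
| .5 | .075 | 4.2% | 78.6% | 80.8% | 2.2 |
| .8 | .172 | 3.1% | 75.1% | 80.8% | 5.7 |

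In this version the total variance is 1 + v. At b = .8 the standardised effect is 0.5/√1.1325 = 0.47 and the correlation 0.6/√1.1325 = 0.56, so the plan's inputs no longer hold.

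**Step 5: simulation** (82 patients, 58/24, balanced within gender, 12,000 runs per cell). The t test with finite degrees of freedom lowers all power figures somewhat.
- On-top version, power without vs with gender: 78.8% vs 79.7%, 77.4% vs 79.8% and 72.8% vs 78.9% for b = .3, .5 and .8. Type I error without gender: 4.6%, 4.0% and 3.2%. At b = 0: 78.7% vs 78.6%.
- Contained version, power without vs with gender: 79.4% vs 80.4%, 79.9% vs 82.0% and 82.8% vs 88.1%.

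Actual permuted blocks (sizes 4 and 6 assumed, 50% or 70% of patients in one gender) give the same picture. At r² = .05, type I error is about 4.2% and power 79.7–79.8% vs 81.1–81.2%. At r² = .10, type I error is 3.7–3.9% and power 79.8–80.6% vs 82.6–83.3%.

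All of this uses the single post-treatment comparison on which the sample size rests, with no treatment-by-gender interaction.

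**The case against.** The strongest reply is that nothing invalid happens. The analysis model matches the sample size model, the error is on the safe side, and the secondary hypotheses are declared exploratory. No section shows that gender predicts the CDRS-R, the BDI-II or any biomarker. For small effects the power forgone is about 1 point, and the .8 SD case, where gender explains some 17–21% of residual variance, has no basis in the documents. All of this stands. It limits the point to a conditional loss of efficiency.

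A reader might infer from the 72.8% in Step 5 that the trial is underpowered. The documents do not support that. The figure arises only when gender variance is added to the planned variance. The plan takes its correlation from the pilot study and mentions no gender adjustment, so the natural reading is that gender variance is already inside the planned SD and correlation; power without gender then stays at about 79% or above in the simulations.

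A reader might also take it as established that the endocrine and growth-factor outcomes are affected. That too depends on gender being prognostic for them, on which the documents are silent.

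It could be said that a fuller analysis plan may list the strata. But the article names its covariate for every ANCOVA, so this is a choice it fixes rather than a detail it leaves open.

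**Conclusion.** The mismatch between design and analysis is real: gender determines the randomisation and is absent from every stated model. Its consequence is conditional. For assumed gender effects of .3, .5 and .8 SD beyond baseline, the true type I error is about 4.5%, 4% and 3% instead of 5%, and about 1, 2.5 and 6 points of attainable power are forgone. These sizes rest on an assumed 58/24 gender split and on effect sizes that the documents do not give; at zero effect there is no loss. Omitting gender does not inflate type I error or bias the estimate, and it does not by itself take the trial materially below its planned power. The change is worth making because it costs almost nothing and aligns the analysis with the randomisation.

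**What to change.** In the Statistical analysis section, add gender, as the randomisation stratum, as a fixed between-subjects factor next to the baseline score in the primary and all secondary ANCOVAs. Specify it before unblinding, so that it is not a covariate chosen after the results are seen. The variable is already recorded for randomisation and sex is among the demographic data. The cost is one degree of freedom, about 0.1 point of power if gender is not prognostic (78.7% vs 78.6% in the simulation). The sample size does not change.

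### A normality check can replace the primary baseline-adjusted ANCOVA with an unnamed non-parametric procedure; if that is an unadjusted rank test, the covariate behind 41 per group is lost

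*Protocol article*

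**What the plan says.** Under Statistical analysis, the article states that "separate 2 × 3 (hypothesis A, E, F)/2 × 2 (hypothesis C, D) mixed ANCOVAs will be conducted", so the primary hypothesis (A) is tested by a mixed ANCOVA. It adds: "As covariate, patients’ baseline scores of each specific parameter will be used". Then comes an assumption check, "ANCOVA assumptions will be explored", and the rule at issue: "In case of violations of normality assumption, appropriate non-parametric procedures will be used".

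The rule covers primary and secondary outcomes alike. It names neither the check nor the replacement, and does not say whether the replacement keeps or drops the baseline score. The same paragraph treats unequal variances and non-sphericity more mildly: the F-test is adjusted and the model stays. Only non-normality replaces the model. Effect sizes are to be eta-squared and Cohen's d, both based on means.

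Under Sample size calculation, the article says: "Participants’ CDRS-R scores at baseline will be included in the model as covariate". It takes the t-test sample size, multiplies it by (1 − ρ²) with ρ = .6, and arrives at 41 per group.

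**The concern.** The sample size and the fallback rule pull in different directions. The number of patients was cut by about a third on the strength of a covariate, while the analysis section allows the model that holds this covariate to be replaced after the data have been examined. The rank tests most often used in practice (Mann-Whitney, Wilcoxon, Friedman) take no covariate. If one of them is used, the trial is analysed at a size that suits only the adjusted analysis.

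The rule could well be triggered. Entry requires a CDRS-R score of at least 40, and the enrolment score is the only pre-treatment CDRS-R assessment in the Data collection and timeline section. The baseline scores are therefore cut off from below, and a check on raw scores could fail even if the model residuals behave well. CRP values below 3 mg/l are set to 0, so CRP is very unlikely to look normal.

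The question would change too: a rank test does not estimate the mean difference for which d = .5 was specified.

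**Working it through.** **Inputs.** From Sample size calculation: d = .5, alpha 5%, power 80%, ρ = .6, 41 per group. The article does not state whether the test is two-sided. Two-sided is assumed because the hypothesis is non-directional and because only a two-sided test reproduces 41.

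**The plan's figure.**
- Two-sided two-sample t test, d = .5, 80% power (non-central t): n = 63.77, so 64 per group.
- Factor 1 − ρ² = 1 − 0.36 = 0.64.
- 64 × 0.64 = 40.96, so 41 per group and N = 82. This agrees with the article.
- One-sided, 51 × 0.64 = 32.6, so 33 per group. This does not agree.

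**Power at 41 per group by formula, normal errors, post-treatment SD set to 1.**
- ANCOVA: residual SD = √0.64 = 0.8; standardized difference 0.5/0.8 = 0.625; divided by √(2/41) = 0.221 this is 2.83; Φ(2.83 − 1.96) = 0.81.
- Unadjusted t test on post scores: 0.61 (non-central t).
- Mann-Whitney on post scores: relative efficiency 3/π = 0.955, effective n = 41 × 0.955 = 39.2, power 0.59. For 80% power, 63.77/0.955 = 66.8, so 67 per group.
- Mann-Whitney on change scores: SD of change = √(2 × (1 − 0.6)) = 0.894; 0.5/0.894 = 0.559; power 0.69. For 80% power, 51.21/0.955 = 53.6, so 54 per group.

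**Simulation.** There were 6,000 runs per scenario with 41 per group and ρ = .6. Errors were normal, gamma (shape 2) or lognormal (log-SD 0.6), scaled to the same variance. The skewed shapes are illustrative.

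| Power at d = .5 | Normal | Gamma | Lognormal |
|---|---|---|---|
| ANCOVA | 0.80 | 0.79 | 0.80 |
| Mann-Whitney, post score | 0.59 | 0.64 | 0.69 |
| Mann-Whitney, change score | 0.69 | 0.77 | 0.82 |
| Rank ANCOVA (Quade) | 0.77 | 0.83 | 0.89 |

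- Type I error of ANCOVA: 0.048, 0.053 and 0.050 in the three scenarios.
- Type I error with a fixed gate (Shapiro-Wilk on residuals at 5%, then one fixed rank test, either Mann-Whitney on post scores or Quade): 0.047–0.053.
- The gate fired in over 99% of runs with skewed errors, so there the gated analysis has the power of the fallback: 0.64 and 0.69 if that is Mann-Whitney on post scores.
- With a true effect, ANCOVA and Mann-Whitney on post scores disagreed on significance in 23–25% of runs.

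**The case against.** The strongest reply is that the article never says the baseline is dropped. It promises only appropriate procedures. The primary endpoint is a two-group comparison from baseline to end of treatment with one covariate, for which a rank ANCOVA is available. That stands: the power loss depends on which procedure is chosen, and with skewed errors a rank ANCOVA has more power than ANCOVA.

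Second, 59% assumes normal errors, whereas the rule is meant for non-normal ones. That stands as well, so the figure to weigh is mainly 64–69% for the unadjusted post-score test. It is still well below the 79–80% for ANCOVA on the same data. A change-score rank test loses little under skewness (77–82%).

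Third, the choice of normality test, threshold and replacement may be left to an analysis plan that is not shown. Their absence is indeed no fault. The point concerns the rule that is stated: it lets a check override the primary model, and naming the check elsewhere would not remove that.

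Fourth, the statistician is blinded to treatment groups. This limits a choice driven by results, but it does not restore a lost covariate or fix the effect measure.

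**Conclusion.** The rule is badly fixed and should be changed before the data are analysed. It allows the covariate that justifies 41 rather than 64 per group to be lost. At 41 per group, power would be about 59% (normal errors) or 64–69% (skewed errors) for an unadjusted post-score rank test, and about 69% or 77–82% for a change-score rank test. A rank ANCOVA would lose little or nothing. Because ANCOVA holds its type I error near 5% under skewed errors at this size, the switch protects nothing that needs protecting.

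Three stronger readings are not supported:
- A reader might infer that the plan abandons baseline adjustment. The text leaves this open.
- A reader might infer that the false-positive rate is inflated. A fixed gate with one fixed fallback keeps it near 5%. Picking the better of ANCOVA and Mann-Whitney by result would give 7–9%, and the best of all four tests 10–12%, but the article describes no such picking.
- A reader might infer that adjustment for the gender stratum is lost. The planned model names only the baseline score as covariate.

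The figures assume a two-sided test, d on the post-treatment SD scale, equal variances and the illustrative error shapes. They refer to the baseline-to-end-of-treatment ANCOVA of the sample size section, not to the full 2 × 3 mixed model.

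**What to change.** State that the baseline-adjusted ANCOVA of CDRS-R remains the primary analysis whatever the normality check shows, with bootstrap or heteroscedasticity-consistent standard errors if needed. Name a baseline-adjusted rank analysis, such as Quade's, as a sensitivity analysis only.

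For the skewed, strictly positive biomarkers (BDNF, IGF-1, TNF-alpha, IL-6 and mean cortisol), pre-specify baseline-adjusted ANCOVA on the log scale. Do not log CRP, which is set to 0 below 3 mg/l, or the cortisol increase over 30 minutes, which can be zero or negative. Use a baseline-adjusted rank or bootstrap analysis for these two.

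The cost is a few sentences and slightly more analysis work, with no change to the sample size or data collection. The small downside is that log-scale results are ratios of geometric means and need a line of explanation.
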